| **Outcome (s)** | The primary study outcomes will be 1) number of sessions of PM+ attended (acceptance of the program = >50% of sessions attended; feasability within the local context = ≥ 1 session attended and offered and participants’ and providers’ qualitative feedback) and 2) improve their mental health status (overall mental health symptoms by SRQ-20 <7; Hopkins Symtpoms checklist reduction (% of cutoff <1.0.6),  Secondary outcomes: Patient Health Questionnaire (PHQ-9) (0-27; cutoff score, >10) for depressive symptoms; Generalized Anxiety Disorder Scale (GAD-7) score range, 0-21; cutoff score, >10) for generalized anxiety symptoms; Psychlops, psychological outcome profiles (designed to evaluate problem management plus intervention) and World bank toolkit on child-mother relationship. |
| **Study Design** | Randomised control trial |
| **Inclusion/Exclusion Criteria** | All mothers enrolled in Zamcharts clinical trial (n=790) with SRQ-20>7.  Exclusion criteria:   - Mothers who plan to migrate out of the study area within 6 months of the enrolment date - Mothers with severe substance use symptoms, bipolar disorder or squizophrenia - Mothers receiving psychotherapy elsewhere |
| **Measurements and Procedures** | From the total of 265 mothers residing in Lusaka district participating in the ZamCharts study and with mental health needs, we will divide them into two groups:  a control group a intervention group  All women will be called for a screening interview and then, if eligible, invited to receive a baseline interview followed by the intervention (provided in health facilities, by phone and at home) at the beginning and an endline interview at the end of the study.  Families in the intervention group will receive a locally adapted version of the Problem-Management Puls intervention developed by WHO after the baseline interview that allows them to better manage life stressors. The intervention will be provided by trained community health workers, started in groups (1^st^ session) and then continued individually by phone, or in-person at health facilities or at women’s home.  Severe cases will be referred to psychiatry services to evaluate need of antidepressants. |
| **Study Product/Intervention according to KlinV, if applicable** | This study will test an intervention: Problem Management+For Moms (PM+FM) program to reduce mental health symptoms among women and increase mother-child interaction |

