| **Comparator(s) (if applicable)** | The comparator for the interventions is standard local caregiving (no intervention) among mothers participating in the Zamcharts clinical trial |
| **Study Duration** | 9 Months |
| **Participants** | A total of 265 caregivers and their children are expected to participate in the study. |
| **Study Schedule** | Sept. 2022: study setup, software development and IRB approval. Identification of WCW  Sept. 2022 – Nov. 2022: Training of 3-5 WCW  Nov. 2022: Enrollment of participants. Screening.  Dec. 2022 – April 2023: implementation of interventions  April 2023: Endline assessments  May 2023 - December 2023: Data analysis & dissemination |
| **Study Centre(s)** | The study will be coordinated by the PIs, and implemented by Innovations for Poverty Action Zambia in direct collaboration with the Zambian Ministry of Health and the department of psychiatry of the University Teaching Hospital in Lusaka. |
| **Statistical Considerations & Power calculations** | The study is statistically powered to detect a 0.25 SD improvement in SRQ-20 over an 6-month period between mothers receiving the PM+FM and mothers not receiving the intervention, assuming α=0.05, a follow-up rate of 85% (attrition < 15%), and an intra-class correlation coefficient (ICC) of 0.05 . The estimated improvement is based on the results from similar studies. |
| **Ethical Statement** | This study will be conducted in compliance with the protocol, the current version of the Declaration of Helsinki, KFPE principles for transboundary research as well as all national legal and regulatory requirements. |

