## Objectives and purpose

The long-term goal of this pilot study is to implement, if found effective, the EM-PM+ intervention within the primary care health system at the national level.

Primary objective**.** We aim to design, test and implement an evidence-based pilot mental health care program integrated within the primary health system for reducing mental health burden among mothers in Lusaka

Secondary objectives**.**

a. To evaluate the acceptability, feasibility and potential efficacy of a culturally sensible evidence-based intervention, the Expanded for Moms-Problem Management Plus (EM-PM+) in reducing mental health symptoms and promoting positive maternal-child relationship among women taking care of young children in Lusaka, Zambia compared to the best locally available care in reducing mental health burden among mothers in Lusaka and improving child development.

c. To build local capacity on mental health access in Lusaka for long-term impact.

e. To produce and disseminate high-quality international scientific publications with the highest ethical standards on the project findings to improve the evidence of mental health interventions in LMICs.

We hypothesize that 1) the EM-PM+ will be accepted by offered individuals (measured as >50% of sessions attended, satisfaction measure and qualitative feedback), 2) the EM-PM+ is feasible within the local context (measured by ≥ 1 session attended and offered and participants’ and providers’ qualitative feedback), 3) individuals receiving the EM-PM+ intervention will improve their wellbeing through improvement of mental health status and maternal-child relationship.

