# Study design

We propose to conduct a trial with mothers in Lusaka district. This area was selected to ensure feasibility of the study. Lusaka is an urban area with relatively easy access to care and transportation.

This is a pilot study nested within the “THE IMPACT OF GROWTHCHARTS ON STUNTING AND CAREGIVER AWARENESS: RESEARCH AND POLICY ENGAGEMENT FOR POTENTIAL SCALING (REF. NO. 1411-2020)” clinical trial using a mix-methods analysis. 790 caregiver-child dyads were enrolled in this study in Lusaka in 2021; 30% of these women displayed mild to severe symptoms of depression and/or anxiety (SRQ-20 ≥ 8). For this feasibility study, we will randomly select women from this subgroup. All selected women will be contacted and reassessed with the Self-Reporting Questionnaire (SRQ-20) and further assessed using the Hopkins Symptoms Checklist-25 items^11-13^.

Final ***eligibility*** will be determined by 1) SRQ-20 >7 (clinically significant symptoms of depression or/anxiety anxiety), 2) women with 1 hour a week availability not planning to move within the next 6 months, 3) capacity to consent and 4) not receiving current mental health care. Individuals with active suicidal ideation (determined by Paykel scale^14^), severe substance use (ACOK-SUD >4),^15^ mania or psychotic symptoms^16^ will be excluded and referred to primary care provider or partnering psychiatrist (for emergency cases). We expect that around 70 caregivers will meet the inclusion criteria for the mental health feasibility study. All selected women from the intervention group will be contacted and reassessed with the Self-Reporting Questionnaire (SRQ-20) and the Hopkins Symptoms Checklist 25.

Eligible individuals will continue with a Baseline interview to assess main outcome measures. We plan to focus on engaging participants in each of the research components of the trial (assessments and sessions) through systematic engagement protocol including regular calls to participants and home visits after two weeks of non-responsiveness. All eligible subjects will be randomized with probability of 0.5 to either treatment or control group. Randomization will be based on a random draw generated by the senior author (GF) using the Stata SE 16.0 statistical software package.

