| Session 3 | Symptom’s assessment. Managing Problems (Problem-solving technique), “get going, keep doing” strategies (Behavioral activation). Managing Stress strategy and mindfulness practice. |
| Session 4 | Managing Problems: understanding unhelpful thoughts. Positive upbringing strategies. Stress management and mindfulness practice. |
| Session 5 | Symptom’s assessment. Importance of support for positive upbringing and stress management. Strengthening social support. Mindfulness practice. |
| Session 6 | Effective communication skills, Mindfulness practice |
| Session 7 | Symptoms’ assessment. Improving healthy habits for me and my child (nutrition, sleep, and substance use). Mindfulness practice. |
| Session 8 | Positive thinking and self-compassion practice. Mindfulness practice. |
| Session 9 | Review of the techniques. Staying Well and Looking to the future (Self-care plan). Mindfulness practice. |
| Session 10 | Review of self-care plan. Social resources and referral. Mindfulness practice. Closure and Ending the programme. |

- 2 booster sessions can be delivered to accommodate urgent needs and/or consolidate core content of the program (i.e. problem management and self-care plan).
- **Management of Severe cases:** Cases found to be severe in mental health symptoms or substance use symptoms, will be referred to our collaborating team of psychiatrists and psychologists from UTH in Lusaka, lead by [name]. Medication prescription and monitoring will be tracked by the research team. Pharmacological treatment (indicated by the psychiatrist) will be subsidized by the project in case participant cannot afford it.

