### Comparator

The comparator (control group) will receive no intervention.

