## Description of statistical methods

First, we will begin with descriptive analysis of all data by site, using means, variances, quartiles, and graphical assessments of the distribution and skewness of the data. We will describe feasibility and acceptability measures at the participant level.

Then, we will proceed with a pre-post intervention analysis using the Hopkins Symptoms Checklist as a main outcome to compare mental health symptoms before and after receiving the intervention. Moreover, on a second phase, we will calculate effect sizes and trends of effectiveness between intervention group and the non-treated group from the parent trial using endline data from parent trial.

We will use standard linear regression models to assess the impact of the intervention arm on mother’s mental health and mother-child relationship. The intervention outcome variable will be SRQ-20 used as a dichotomous variable with the cutoff at seven. Separate models will be estimated with and without baseline covariates.

The feasibility, acceptability, and difficulties and successes in carrying out research and intervention activities will be explored through a mix-methods analysis including dosage analysis (attendance to the intervention’s sessions) and semi-structured interviews with the participants and focus group with intervention’s providers. The burden of completing the assessments and PM+FM on the time and effort of participants, satisfaction with the intervention, and barriers and facilitators to adherence will be explored through semi-structured interviews with all the participants enrolled in the intervention arm (including participants that have dropped out). Qualitative data resulting from the open-ended questions to participants and focus groups with WCHWs will be transcribed, coded and analysed using a thematic approach to inform on feasibility, acceptability, and explain the potential efficacy of the PM+FM intervention

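### The referral rule for severe cases names no arm and sits under the experimental intervention, so the Protocol does not secure referral for severely depressed or anxious women allocated to control

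*Protocol*

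**What the plan says.** The Protocol states the referral rule twice.

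- Synopsis, Measurements and Procedures, straight after the description of what the intervention group receives: "Severe cases will be referred to psychiatry services to evaluate need of antidepressants".
- Experimental intervention (treatment / medical device), as a bullet after the session table and the booster sessions: "Cases found to be severe in mental health symptoms or substance use symptoms, will be referred to our collaborating team of psychiatrists and psychologists". The bullet adds that the research team tracks prescriptions, and continues: "Pharmacological treatment (indicated by the psychiatrist) will be subsidized by the project in case participant cannot afford it".

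Neither place names an arm. The control condition is described in four places:

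- Comparator: "The comparator (control group) will receive no intervention".
- Synopsis, Comparator(s): "The comparator for the interventions is standard local caregiving (no intervention" (the bracket closes just after these words).
- Objectives and purpose: "compared to the best locally available care in reducing mental health burden among mothers in Lusaka".
- Description of statistical methods: a comparison "between intervention group and the non-treated group from the parent trial".

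On assessment before randomisation, Study design says: "All selected women will be contacted and reassessed with the Self-Reporting Questionnaire (SRQ-20) and further assessed using the Hopkins Symptoms Checklist-25 items". A later sentence in the same section describes reassessment with the same two instruments for the intervention group only.

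**The concern.** Women with severe depression or anxiety can enter the trial, and the inclusion criteria require that they are not already in mental health treatment. If such a woman is allocated to control, the Protocol states no action for her until endline, 5 months after baseline (Study duration) or 6 months after enrolment (Primary endpoint). The scientific justification itself calls public mental health provision scarce and drug treatment the first option for severe cases.

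Two things are at stake. The first is the safety of severe controls. The second is what the arm comparison measures. If referral and subsidised drugs reach one arm only, the contrast is PM+FM plus psychiatric care against neither, although the intervention section says a single intervention is assessed. Because no arm is named, staff could also refer differently by arm. The Protocol does not say whose prescriptions are tracked, so co-treatment by arm might not be reportable.

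**Working it through.** This is mainly a question of reading sections together. The arithmetic only illustrates scale.

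**1. Does any other rule cover severe controls?**

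- Screening referral (Study design; Exclusion criteria) covers only women who are excluded: those with suicidal ideation, severe substance use, mania or psychosis. Severe depression or anxiety without these features is not an exclusion, so these women are randomised, each with probability 0.5.
- The two safety headings (HRO Art. 20 and Art. 21) both point to 10.2. Section 10.2, Monitoring, covers only electronic monitoring of the surveys.
- Emergency and referral procedures appear under training and supervision, as course content for the workers who deliver the intervention.

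None of these reaches a severe woman in control.

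**2. Would an arm-neutral rule work equally in both arms?**

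The session table puts a symptom assessment in sessions 1, 3, 5 and 7, and severe cases are discussed in the delivery supervision. The Protocol describes no symptom assessment of controls between baseline and endline. A woman who worsens would therefore be found mainly in the intervention arm.

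**3. Do the comparator descriptions agree?**

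Three are compatible. The Synopsis equates standard local care with no intervention, and the Comparator and statistical methods sections can both be read as no PM+FM. The objectives differ: the best care available locally is not the same as nothing. None of the four mentions referral by the study.

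**4. How many women might be affected?**

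Inputs: a severe share of 25% (the team's own data) or 30% (a general figure), both from the scientific justification and both before the trial's exclusions; about 70 eligible women (Exclusion criteria); 100 per arm for analysis (section 7.2).

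Severe controls = controls × severe share:

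- 35 × 0.25 = 8.75 and 35 × 0.30 = 10.5, about 9 to 11.
- 100 × 0.25 = 25 and 100 × 0.30 = 30.

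A check that does not use that share: with k severe women randomised, the chance that at least one goes to control is 1 − 0.5^k. For k = 3, 5 and 7 this is 87.5%, 96.9% and 99.2%. With a fixed 35/35 split and k = 5, it is 1 − C(35,5)/C(70,5) = 1 − 324632/12103014 = 97.3%. The values of k are assumptions; k = 5 is 7.1% of 70.

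**5. How much could drugs add to the arm difference?**

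Contribution = severe share × gain in remission among severe women from one-arm referral. The Protocol gives no such gain. Assumed gains of 10 to 50 points give 0.25 × 10 = 2.5 to 0.30 × 50 = 15 points, against the 20-point difference in section 7.2. The range is too wide to support an estimate.

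**6. Is the sample size affected?**

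No. With 100 per arm, two-sided alpha 0.05 (sidedness assumed) and an assumed control prevalence of 0.55 to 0.65, power is 0.812 to 0.816 for 20 points and 0.908 to 0.913 for 23 points. This agrees with the stated 0.8 and 0.9.

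**The case against.** The strongest reply is that the wording is arm-neutral. The Synopsis sentence is unrestricted and sits in a row that also covers screening of all women. The treatment-section bullet speaks of cases and of a participant, and the list it belongs to also holds trial logistics such as training and supervision. It even mentions severe substance use, which is an exclusion before randomisation, so it may be study-wide case handling. That stands as far as intent goes: a reader might infer that controls are denied referral, and the documents do not support this. The one-arm reading rests on where the bullet is placed, on the Comparator section, and on the scientific justification, which presents treatment at every severity as part of the multi-level intervention under test.

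A reader might also infer that the study will knowingly hold women it has measured as severe. That goes too far. The Protocol gives no SRQ-20 or HSCL-25 cut-off for severe, the eligibility threshold marks caseness only, and Study design is inconsistent about who is reassessed.

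Nor do the four comparator descriptions all contradict each other; only the objectives stand clearly apart.

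Finally, a severity cut-off and co-medication tables often sit in procedures or in the SAP, and the emergency procedures are not shown. That is fair for the detail. It does not answer the main point, because which arm a safety rule applies to, and what the comparator is, belong in the Protocol, and there the text pulls in two directions.

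**Conclusion.** The point holds as a gap in what the Protocol secures, and it should be fixed. Followed by its own structure, the plan gives referral and subsidised medication to the intervention arm and nothing to control. Read as arm-neutral, it still detects severity mainly in the intervention arm. No section settles the matter for severe women who are eligible, untreated and allocated to control.

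The size is open. The 9 to 30 severe controls are illustrations that apply pre-exclusion shares to a post-exclusion sample, and the 97% shows only that even a few severe women would almost certainly include a control. A reader might infer that psychiatric drugs explain a given part of any arm difference; the documents allow no such figure. Confidence is medium, because both-arm referral may well be what the sponsor intends.

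**What to change.** 1. In the Management of Severe cases bullet and in the Comparator section, state that any woman found severe at screening, baseline or endline is referred to the psychiatric team regardless of arm. Define severe by a stated SRQ-20 or HSCL-25 cut-off, and state that the instrument is measured in all women before randomisation.
2. Use one comparator description in the Synopsis, Objectives and purpose, Comparator and Description of statistical methods: standard local care, no PM+FM, with referral of severe cases.
3. Record psychiatric contact and psychotropic medication in the same way in both arms at endline, and report them by arm. Control endline data are described as coming from the parent trial, so the questions must be in that survey too.
4. Whether to extend the medication subsidy to controls is a cost and design choice for the sponsor. If it stays in the intervention arm only, describe the contrast as PM+FM plus psychiatric referral and medication in the intervention section, hypothesis 3 and the conclusions.

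The cost is Protocol wording, a few endline questions, and some extra referrals to a psychiatric team already in place, plus drug costs if the subsidy is extended. Treating severe controls may narrow the arm difference. That is acceptable in a pilot whose efficacy analysis section 7.2 calls exploratory. No sample-size figure changes.

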### Comparator

The comparator (control group) will receive no intervention.

# Description of data management

## Specification of source documents

All source documents will be created in English. Data collection tools (screening, baseline and endline survey forms and informed consent forms) will be translated to local language. Back-translations will be made to ensure accuracy of translations.

## Data management system

All data will be collected and stored electronically using the Survey Collect (SurveyCTO) software. Survey CTO is tool intended to facilitate mobile data collection services. It consists of an Android app that replaces paper forms used in survey-based data gathering. It supports a wide range of questions and answer types and can be utilized without network connectivity. All data collection will occur offline on password protected Android devices. Data connectivity will only be used to send data collected in the field. Data storage will be on a local secured computer in Zambia and on ServeyCTO’s secure servers.

Data storage will be on a local secured server at IPA Zambia.

## Data security, access, archiving and back up

Project data is only accessible to authorised personnel who require data to fulfil their duties within the scope of the research project. On the eCFRs and other project specific documents, participants are only identified by a unique participant number. Data and databases will not be shared with the public and will only be available (fully anonymised) for verification purposes of authorities or scientific journals (as condition to publish results) – on request only. All study data will be archived for a minimum of ten years after study completion.

# Statistics

## Hypothesis

In this sub-project of the ZamCharts trial, we wish to assess the following three hypotheses

1) the PM+FM will be accepted by offered individuals (measured as >50% of sessions attended, satisfaction measure and qualitative feedback),

2) the PM+FM is feasible within the local context (measured by ≥ 1 session attended and offered and participants’ and providers’ qualitative feedback),

3) individuals receiving the PM+FM intervention will improve their wellbeing through improvement of mental health status and maternal-child relationship.

## 7.2. Sample size calculation

This is a pilot study nested within the “The impact of growthcharts on stunting and caregiver awareness: research and policy engagement for potential scaling (ref. no. 1411-2020)” clinical trial. 800 caregiver-child dyads were enrolled in this study in Lusaka in 2021; 28% of these women displayed mild to severe symptoms of depression and/or anxiety (SRQ-20 ≥ 8). For this feasibility study, 30% of the women enrolled in the parent trial displayed mild to severe symptoms of depression and/or anxiety (SRQ-20 ≥8). For this study, we expect an attrition rate of 13% based on previous studies. With an expected analytical sample size of 100 women per arm we are powered to detect an intent-to-treat difference of 20 percentage points in the prevalence of depression at endline with power 0.8, and 23 percentage point difference in depression with power 0.9. We are aware that for the current trial we are not powered to detect small effect size. Thus, we will only explore the efficacy of the intervention to generate some preliminary efficacy estimates that will serve us to power and elucidate the needed sample size for a larger effectiveness trial.

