| WHODAS2.0 | World Health Organization Disability Assessment |
| SRQ-20 | Self-Report Questionnaire |
| ACOK | Screen for Co-Occuring Disorders |
| PSYCHLOPS | Psychological Outcome Profiles |

1. **Synopsis**

| **Sponsor/Sponsor-Investigator** | [name] |
| --- | --- |
| **Co-Principal Investigator** | [name] |
| **Study Title** | The impact of PM+FM intervention on improving mother’s mental health in Zambia |
| **Short Title/Study ID** | PM+FM |
| **Protocol Version and Date** | Version 1.1; 29.10.2022 |
| **Trial Registration** | Pending – will be registered on Clinicaltrials.gov |
| **Study Category with** **Rationale** | Other Clinical Trials, Category A  Rationale:  - Research project in which persons are prospectively assigned to a health-related intervention in order to investigate its effects on health or on the structure and function of the human body.  - Definition of Health (WHO): Health is a state of complete physical, mental and social well-being and not merely the absence of disease or infirmity |
| **Clinical Phase** | Not applicable. Not a clinical trial with drugs. |
| **Background and Rationale** | CMHD are particularly prevalent among women, posing a major threat to their own and their children’s wellbeing. In Zambia, our research team found that around 28% of women suffer from anxiety or depression.  Despite the high prevalence of CMHD and the existence of effective treatments, interventions supporting women living in low-resourced settings remain limited. Recent community-based programs have succeeded in cost-effectively tackling minor mental health problems, but have not helped individuals with severe symptoms.  This study builds on a parent study (Zamcharts), which identified a high prevalence of women with anxiety and/or depression. We propose to design, test and validate a community-based intervention nested within the public primary health system in Zambia, as a mental health care delivery platform to identify and treat women with mild-to-severe CMHDs. We aim to demonstrate the impact of integrating high-quality mental health care in the national system. |
| **Objective(s)** | To 1) adapt the Problem Management plus program to sub-Saharan mothers living in Zambia and to 2) assess the acceptability, feasibility and potential efficacy of the resulting intervention in reducing mental health symptoms and promoting positive maternal-child relationship among women taking care of young children in Lusaka, Zambia. |

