## Primary and secondary endpoint

### Primary endpoint

The primary endpoint will be SRQ-20 = or < 7 6 months after enrollment in the trial and/or HSCL-25 <1.06 6 months after enrollment.

We will also collect data on attendance rates to assess feasibility and acceptability throughout the deployment of the intervention:

- Feasibility will be assessed by the percentage of participants completing 1 or more sessions of the intervention and through a focus group with the intervention providers.
- Acceptability will be evaluated using the percentage of participants completing the program (≥50% sessions completed) together with qualitative feedback from participants and providers through a semi-structured interview at the end of the intervention and participants’ feedback from a semi-structured interview at the end of the intervention.

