### Primary Analysis

The primary analysis of program feasibility, acceptability and pre-post treatment analysis will be conducted directly be the PI of the parent study (GF) and the present sub-study (IFB) with support from the co-investigators. Effectiveness analysis will be done by the PI of the parent study (CF). This analysis will be intention-to-treat, and thus not adjust for protocol compliance.

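### Mental-health recovery is a primary endpoint that the Synopsis calls powered, while section 7.2 says efficacy is only explored; no text says which status governs the between-arm result

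*Protocol*

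**What the plan says.** Places that give efficacy primary status:

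- **Primary endpoint section:** "The primary endpoint will be SRQ-20 = or < 7 6 months after enrollment in the trial", and/or HSCL-25 below 1.06 at the same time. Attendance, for feasibility and acceptability, is introduced as additional data.
- **Synopsis, Outcome(s):** the second of two primary outcomes is that mothers "improve their mental health status (overall mental health symptoms by SRQ-20 <7", together with an HSCL criterion. The first is session attendance, covering acceptance and feasibility.
- **Table 1 (Measures and Outcomes):** SRQ-20 is a primary outcome measure beside feasibility and acceptability. HSCL-25 is listed as secondary.
- **Synopsis, Statistical Considerations & Power calculations:** the study is said to be powered for a 0.25 SD improvement in SRQ-20 at 6 months, with alpha 0.05, 85% follow-up and an ICC of 0.05.

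Places that make it exploratory or leave its rank open:

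- **Section 7.2:** the trial is not powered for small effects. "Thus, we will only explore the efficacy of the intervention to generate some preliminary efficacy estimates", to be used in sizing a larger effectiveness trial.
- **Objectives and purpose:** acceptability, feasibility and potential efficacy share one secondary objective.
- **Description of statistical methods and Primary Analysis:** HSCL-25 is the main outcome of a pre-post comparison, and this is named first: "The primary analysis of program feasibility, acceptability and pre-post treatment analysis". The between-group comparison is a second phase.

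**The concern.** A protocol fixes the status of its primary endpoint so that the reading of the result is settled before the data are seen. Here two readings are open. Under the Primary endpoint section, a clear between-arm difference on SRQ-20 is a primary endpoint met and an unclear one is a primary endpoint missed. Under section 7.2 either is a preliminary estimate for planning, with no verdict attached.

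The Synopsis power sentence makes this worse. A reader who meets it first will take a null result as evidence against the programme, because the trial is said to have been able to see a 0.25 SD effect. If it could not, that inference is wrong.

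HSCL-25 adds a further route to an efficacy claim. It is primary in two places, secondary in Table 1, and the main outcome of a pre-post analysis without a control group. A fall in HSCL-25 among treated women could be reported as the primary analysis although it cannot separate the programme from natural recovery or regression to the mean, in women selected for high symptom scores.

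**Working it through.** **Step 1. Reproduce section 7.2.** Inputs stated there: 100 analysed per arm, 20 points with power 0.8, 23 points with power 0.9. Assumed: two-sided alpha 0.05, and a control prevalence at endline, which the protocol does not give.

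Power = Φ{[d − 1.96·√(2p̄(1−p̄)/n)] / √[(p₁(1−p₁)+p₂(1−p₂))/n]}

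- 60% v 40%, n = 100: (0.20 − 1.96 × 0.0707)/0.0693 = 0.886, power 0.81.
- 60% v 37%, n = 100: (0.23 − 1.96 × 0.0707)/0.0688 = 1.33, power 0.91.

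Across assumed control prevalences of 0.30 to 0.90, power for 20 points runs from 0.81 to 0.95. Section 7.2's figures hold at mid-range prevalence. Its caution about small effects also holds: with rates centred on 50%, power is 0.57 for 15 points and 0.29 for 10.

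**Step 2. Check the Synopsis claim of 0.25 SD.** Inputs from the Synopsis: alpha 0.05, 85% follow-up, 265 participants. Assumed: two-sided test, 1:1 split, target power 80% (the Synopsis states none), no covariate adjustment.

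- Needed per arm: n = 2(1.960 + 0.842)²/0.25² = 2 × 7.85/0.0625 ≈ 252.
- Available per arm: 265/2 × 0.85 = 112.6.
- Power = Φ(0.25·√(n/2) − 1.96). At 112.6: Φ(1.876 − 1.96) = 0.47. At section 7.2's 100 per arm: Φ(1.768 − 1.96) = 0.42.
- Smallest effect with 80% power, 2.80·√(2/n): 0.37 SD at 112.6 per arm and 0.40 SD at 100.

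**Step 3. Add the Synopsis's ICC of 0.05.** No cluster size is given, so it is assumed. With m women per cluster the design effect is 1 + (m − 1) × 0.05. From 112.6 per arm:

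| m | design effect | power for 0.25 SD |
|---|---|---|
| 2 | 1.05 | 0.45 |
| 3 | 1.10 | 0.43 |
| 5 | 1.20 | 0.40 |

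**Step 4. One result under two readings.** Suppose 60% of control and 50% of intervention women remain above the cutoff, with 100 per arm. The difference is 10 points, its standard error √[(0.24 + 0.25)/100] = 0.07, and the 95% CI about −4 to 24 points. As a primary endpoint this would naturally be reported as missed. Under section 7.2 it is a usable planning estimate.

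**The case against.** The strongest reply is that primary does not mean confirmatory. A pilot may name a primary endpoint that it only estimates, and the statistical methods section does speak of effect sizes and trends. The protocol also sets no significance-based success rule, so a verdict of met or missed is something authors might write, not something the text prescribes. That much stands. It does not explain the Synopsis, which says the study is powered for an effect that section 7.2's own sample would detect less than half the time.

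Adjustment for baseline could raise power. To reach 80% with 112.6 per arm, the baseline-endline correlation r would need 1 − r² = 112.6/252 = 0.447, so r of about 0.74. The protocol gives no correlation and makes no such claim.

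Several stronger readings are tempting and are not supported:

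- **That this pilot triggers national roll-out.** The text reads "The long-term goal of this pilot study is to implement, if found effective, the EM-PM+ intervention". That is a long-term goal with a condition on the intervention and no decision rule. The Introduction speaks only of a first step. Pilot, larger trial and scale-up can be read as a sequence; the wording merely leaves the middle step out.
- **That the Synopsis promises proof.** "We aim to demonstrate the impact of integrating high-quality mental health care in the national system" is background text about integrating care, and the Objective(s) row of the same table says potential efficacy.
- **That hypothesis 3 or the Primary Analysis section settles the rank of efficacy.** A pilot can examine a hypothesis without confirming it, and both the pre-post and the effectiveness analyses stand under the Primary Analysis heading.
- **That an effective programme would miss its endpoint about 60% of the time.** This takes the roughly 70 eligible women expected in the Study design and Exclusion criteria sections. At 35 per arm, power for 20 points is 0.39 to 0.55 for assumed control prevalences of 0.30 to 0.90. The conflict between 70 women and 200 analysed is a separate defect and does not measure ambiguity about status.

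**Conclusion.** The contradiction stands in the current text. SRQ-20 recovery is primary in three places and described as powered in the Synopsis, while section 7.2 restricts efficacy to exploration. An analysis plan could not settle this without overriding one of them.

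The powered claim is wrong on the protocol's own figures: about 252 per arm are needed against about 113 or 100 available, so power is 0.42 to 0.47 before clustering. This rests on a two-sided 5% test, an 80% target and no covariate adjustment. Section 7.2's own power figures are sound at mid-range prevalence and are not in question.

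The consequence is freedom to choose the reading after the data are seen. A reader might infer that the plan commits to scale-up on this result; it does not. The correction is one of wording, but it changes what the trial may conclude.

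**What to change.** Before endline data are seen, give efficacy one status throughout:

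1. Keep feasibility and acceptability, already primary in the Synopsis and Table 1, as the primary outcomes. Reword the Primary endpoint section to match, and move them out of the secondary objectives in Objectives and purpose.
2. Label as exploratory efficacy the between-arm SRQ-20 comparison, the HSCL-25 below 1.06 criterion, and the uncontrolled HSCL-25 pre-post analysis in Description of statistical methods and Primary Analysis. Report each as an estimate with a 95% confidence interval and no verdict of effectiveness.
3. Delete the Synopsis sentence on 0.25 SD, or restate it to agree with section 7.2.
4. In Objectives and purpose, say that national implementation would follow the larger effectiveness trial that section 7.2 foresees.

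The cost is protocol and registry wording; no procedure, visit or sample changes. The sponsor gives up an effectiveness claim from this pilot, which section 7.2 already concedes.
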